### Assignment of interventions

Permuted varying block randomisation with 1:1 allocation ratio stratified by trial site was generated using Stata V.18 (StataCorp. 2023. Stata Statistical Software: Release 18., StataCorp) by an independent statistician, not involved in the recruitment process. Varying block size was used to minimise predictability due to the open-label nature of the trial. The randomisation scheme will be implemented using the interactive web randomisation feature of REDCap managed centrally at the sponsor institute. Following informed consent and baseline data collection, the research coordinator will log into REDCap using site specific user credentials to randomise the participant. The group allocation will be made available on confirmation of eligibility and informed consent. Automatic real-time system-generated notification of the group assignment will be sent to the trial investigators and research coordinator. All participants will be in the trial for 6 months after enrolment. They will be followed up at 3 and 6 months after randomisation.

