**Methods and analysis:**

Consecutive adults undergoing partial or total, unilateral or bilateral knee arthroplasty who can use a smart phone will be invited to participate in this trial. Consenting individuals will be randomised to either an app-supported intervention or a usual home-based rehabilitation which typically consists of provision of oral or written instructions at discharge and follow-up check-up with the surgeon or physiotherapist at their discretion or as per individual need. We aim to recruit 300 individuals over a period of eighteen months. The primary objective is to compare patient-reported knee function between the two groups at 3 and 6 months postsurgery. Secondary objectives are to compare patient-reported outcomes (pain and activity), performance-based outcomes (lower limb strength and knee function), resource utilisation and quality of life. Fidelity of implementation, end-user experiences and challenges in implementing this intervention will be measured using both quantitative and qualitative methods. Quantitative data will be analysed in Stata, and group comparisons will be done using mixed effect linear regression. A mixed-methods approach will be used to analyse and interpret the process evaluation data. A modified intention-to-treat approach will be taken, which includes all those who were randomised irrespective of their adherence to trial protocol if they had at least one follow-up visit after enrolment.

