## Methods and analysis

### Trial design

This is a parallel arm 1:1 individual randomised open-label superiority trial with an embedded cost–utility analysis conducted at two tertiary care centres. Patients undergoing knee arthroplasty will be randomly allocated to app-supported or usual care home-based rehabilitation and followed up until 6 months after surgery (figure 1). The trial is registered with the clinical trial registry of India (CTRI/2024/06/068838). The trial recruitment commenced in June 2024 and is planned to finish in December 2025.

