### Eligibility criteria and recruitment

Consecutive patients scheduled for primary knee arthroplasty with the participating orthopaedic surgeon will be screened for eligibility. Patients will be screened at the outpatient orthopaedic surgery clinic or when admitted for the surgery or postsurgery but prior to hospital discharge.

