### Outcomes

Primary outcome: Early recovery of knee function is one of the desired outcomes by patients undergoing knee arthroplasty.^14^ The primary outcome knee function will be assessed using the ADL subdomain of Knee Injury and Osteoarthritis Outcome Score (KOOS). It is a validated tool to evaluate post knee rehabilitation interventions^15^ and will be completed by the trial participants at baseline (before surgery status), 3 and 6 months after surgery in both groups. The total score ranges between 0 and 100 and the minimum clinically important group difference for this domain ranges from −1.5 to 15.5 units.^16^ The KOOS-ADL questionnaire will be self-administered in paper during the follow-up visit by the patient. If the patient is not able to complete it by self, then the family member will assist in eliciting the responses from the patient. In the absence of a family member, an independent assessor, not involved in the intervention implementation and rehabilitation, will administer the questionnaire. The primary comparisons would be to compare the end value of KOOS-ADL score at 3 and 6 months independently between the two groups adjusted for baseline score.

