### Data collection and management

Data will be collected at the physiotherapy clinic of the recruiting hospitals in paper forms at baseline and at 3 and 6 months postrandomisation by a trained research coordinator. Data will be single entered into a web-based electronic data capture system (REDCap) with in-built validation checks and a query management system. Source data verification will be done by the trial manager to check for accuracy against the paper forms. Initially, 100% of forms will be checked and the subsequent percentage of the forms checked will depend on the proportion of transcription errors identified. Data related to cost will be entered into an excel sheet for further processing.

To ensure data quality, periodic data review checks will be done by the trial manager not involved in data collection, using Stata to flag discrepancies that may not be detectable by inbuilt automatic checks. These checks include cross-form logic checks and completeness of critical fields. Queries will be raised in REDCap for the research coordinator to update or respond. A back-up of all data will be done periodically as per the institution server policy. The paper forms, along with informed consent, will be safely secured in a cabinet with restricted access at the Sponsor institute.

Semistructured interviews will be conducted either face-to-face or telephonically from a purposively selected sample of trial participants based on the extent of app usage (users, partial-users, non-users). The interviews will be audio-recorded or written notes will be taken depending on how comfortable the participants are with the audio recording. Participants will be invited for interviews until data saturation is reached. All the healthcare providers involved in the intervention implementation at the hospital will be interviewed. The interviews will be conducted by a member of the research team trained in qualitative interview methods. Qualitative interviews will be transcribed and translated by one of the members of the research team and cross-checked by another member of the team for correctness and appropriateness.

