**Figure 3 F3:**
[figure not shown]
PRagmatic Explanatory Continuum Indicator Summary 2 wheel to demonstrate level of pragmatism of TReAT trial. Eligibility, 3: Eligibility limited to digitally literate individuals, thus limiting the applicability of the results about remote rehabilitation to patients or family members without a device or digital literacy. Recruitment path, 3: Recruiting only eligible patients operated by principal investigator at each site, instead of all patients referred to physiotherapy for post-knee replacement rehabilitation care. Setting, 4: Though only 2 participating referral hospitals across India, they cater to a large representative population in Northern India across socioeconomic status. Organisation intervention, 2.5: Minimal training provided to health care providers but requiring research coordinator support to enrol participants in the application and facilitate follow-up. Flexibility of intervention delivery, 4: The intervention components are delivered as per participant requirement; there is no restriction on concomitant therapies. Flexibility of intervention adherence, 3: In addition to usual care, the research coordinator makes check-in calls to all trial participants to aid on app use and reminders are given to health care providers for video consultation and therapy planning. Follow-up, 2.5: Patients are required to come for trial-related follow-up visits at 3 and 6 months postsurgery which is not part of usual care. Additionally, telephonic check-in calls made between visits to reduce attrition are additional to the trial. Outcome, 4: Patient-reported function is the primary outcome, but is not recorded as part of routine medical records and collected specifically for the trial. Analysis, 4: Modified intention-to-treat approach will be used to account for attrition. TReAT, TeleREhabilitation after knee ArThroplasty.

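### The primary assessments have two time origins: the outcome definition counts 3 and 6 months from surgery, while the visit schedule counts them from randomisation, which may precede surgery.

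*Protocol article*

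**What the plan says.** **Counted from surgery.** The Outcomes section says that KOOS-ADL "will be completed by the trial participants at baseline (before surgery status), 3 and 6 months after surgery in both groups". Other parts agree:

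- The abstract states the primary objective as to "compare patient-reported knee function between the two groups at 3 and 6 months postsurgery".
- Trial design says patients are "followed up until 6 months after surgery".
- The legend to Figure 3 refers to "trial-related follow-up visits at 3 and 6 months postsurgery".
- The strengths and limitations box and the exclusion criterion on attending hospital visits also count from the operation.

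**Counted from randomisation or enrolment.** Assignment of interventions says "All participants will be in the trial for 6 months after enrolment" and then "They will be followed up at 3 and 6 months after randomisation". Data collection and management says that forms are completed "at baseline and at 3 and 6 months postrandomisation by a trained research coordinator".

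**When enrolment can happen.** Eligibility criteria and recruitment says: "Patients will be screened at the outpatient orthopaedic surgery clinic or when admitted for the surgery or postsurgery but prior to hospital discharge". Assignment of interventions places randomisation after consent and baseline data and does not tie it to the operation date. Table 1 (row on timing and amount) says that the intervention may begin on either side of surgery, depending on when the patient is enrolled.

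The article gives no maximum interval from randomisation to surgery and no sentence that reconciles the two clocks.

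**The concern.** A trial needs one definition of when its primary endpoint is measured. Here the outcome definition uses one clock, and the two sections that staff would follow to book visits use another. If every patient were randomised within a day or two of the operation, the difference would be trivial. Because enrolment before surgery is allowed, the gap can vary from patient to patient.

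Time since surgery is part of what this endpoint measures. The Introduction calls rehabilitation essential in the first 3 months, and the Outcomes section justifies the endpoint by early recovery of function. Visits booked from randomisation would put patients at different stages of recovery under the same 3-month label. That would add variance and leave it unclear whether the estimate refers to time since surgery or time since randomisation. The cost analysis uses the same visits to build QALYs at 6 months, so it inherits the ambiguity.

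**Working it through.** **1. The texts side by side**

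| Item | Time origin | Where |
|---|---|---|
| Primary outcome definition | surgery | Outcomes |
| Primary objective | surgery | Abstract |
| Length of follow-up | surgery | Trial design |
| Follow-up visits | surgery | Figure 3 legend; also exclusion criteria and strengths box |
| Follow-up visits | randomisation | Assignment of interventions |
| Data collection | randomisation | Data collection and management |
| End of participation | enrolment | Assignment of interventions |

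These agree only if randomisation and surgery coincide, and the eligibility text does not require that.

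**2. How far the clocks can separate**

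For a patient enrolled after surgery, the protocol bounds the gap: discharge is typically 48–72 hours after the operation (Study setting), so a visit on the randomisation clock is at most about 2–3 days late. For a patient enrolled before surgery there is no stated bound. With an assumed lead of *w* weeks, a visit on the randomisation clock falls at 13.0 − *w* or 26.1 − *w* weeks after surgery:

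| Assumed lead (weeks) | 3-month visit (weeks after surgery) | 6-month visit (weeks after surgery) |
|---|---|---|
| 0 | 13.0 | 26.1 |
| 2 | 11.0 | 24.1 |
| 4 | 9.0 | 22.1 |
| 8 | 5.0 | 18.1 |

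**3. The plan's own sample size, as the reference for power**

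Inputs from Sample size and Statistical methods: effect size 0.40, two-sided alpha 0.025 per time point, power 85%, loss 10%.

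- n per group = 2 × (2.241 + 1.036)² / 0.40² = 134.3, so 135.
- 135 / 0.90 = 150. The stated figure is reproduced.

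The same section names a 7-point difference with SD 15, which is 7/15 = 0.467. An effect size of 0.40 with SD 15 corresponds to 0.40 × 15 = 6 points. Both targets are carried forward below.

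**4. Illustrative cost in variance**

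The protocol gives neither a recovery slope nor a spread of lead times, so both are assumed. The sums also assume that all visits run on the randomisation clock, that recovery is linear near the visit, and that lead time is unrelated to the rest of the outcome variation. Then

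SD = √(15² + (slope × lead-time SD)²).

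Power is from the two-sample t-test (noncentral t) with 135 per group and alpha 0.025.

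| Slope (points/month) | Lead-time SD (months) | Variance ratio | SD | Power, 7 points | Power, 6 points |
|---|---|---|---|---|---|
| none | none | 1 | 15.0 | 0.94 | 0.85 |
| 2 | 0.5 | 1 + 1/225 = 1.004 | 15.03 | 0.94 | 0.85 |
| 4 | 1 | 1 + 16/225 = 1.07 | 15.5 | 0.93 | 0.82 |
| 6 | 1.5 | 1 + 81/225 = 1.36 | 17.5 | 0.85 | 0.71 |

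The range runs from negligible to material, and nothing in the protocol says where in it the trial lies.

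**The case against.** The strongest reply is that the surgery clock has most of the weight. It is in the outcome definition, the abstract, the design section, the exclusion criteria and the Figure 3 legend. The references to randomisation may be loose wording in procedural sections, and the protocol does not show which clock the sites follow. Unequal recovery times arise only if visits are booked from randomisation. This stands, and the point is worded conditionally for that reason.

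A second reply is that long leads are conjecture. The eligibility text describes screening, not randomisation, and Table 1 (row on procedures) has physiotherapists register patients in the app during the hospital stay, before or after the operation. If randomisation happens near registration, the clocks differ by days. This also stands as a reason to expect a small effect. It does not remove the conflict, because Table 1 still lets the intervention start before surgery according to the time of enrolment, and no limit is set.

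A reader might infer four stronger things, which the document does not support:

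- **Bias between arms.** Lead time is fixed largely at enrolment, and randomisation stratified by site balances it in expectation.
- **A shift comparable with the 7-point target.** A month's lead might move one patient's score by several points, but 7 points is a difference between groups, and the lead is shared by both groups.
- **A 6-month postsurgery endpoint that cannot be collected.** That needs a strict reading of the sentence ending participation 6 months after enrolment. Trial design says follow-up runs to 6 months after surgery.
- **An estimate that answers neither question.** If all visits follow one clock, the estimate answers that clock's question. The difficulty is that the document does not say which clock applies.

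**Conclusion.** The protocol is wrong as written on this point: following the two scheduling sections literally would not deliver the endpoint defined under Outcomes for patients randomised before surgery. Confidence in the textual conflict is high.

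The practical size is unknown. It depends on which clock the sites use and on the interval from randomisation to surgery, and the document gives neither. If most patients are randomised during the hospital stay, the effect is small. Under the most adverse assumptions shown, power at 135 per group stays at about 85% for the 7-point difference; it falls to about 71% if the target is read as 6 points. The case for acting rests on the clarity of the primary endpoint and the low cost of correction, not on these assumed power losses.

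**What to change.** 1. In Assignment of interventions and in Data collection and management, replace the references to randomisation and enrolment as the origin for visits and for end of participation with surgery, so that scheduling matches the primary outcome definition.
2. Record the actual date of surgery and of each assessment for every participant. Recruitment began in June 2024, so some visits may already have been made on the other clock; time since surgery can then be reported for them.
3. Reconcile the statements on when app support ends. The App-based rehabilitation text and the timing row of Table 1 count from surgery, while the procedures row of Table 1 counts from enrolment. Which of these applies is for the investigators to settle.

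The cost is a wording amendment and a scheduling change. Final visits may move slightly later for patients enrolled before surgery near the end of recruitment (planned for December 2025, with data collection planned to June 2026).

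A fallback origin for randomised patients whose surgery is cancelled, and sensitivity models using days since surgery, are optional and can be left to the full protocol or SAP. Such models need care: actual time since surgery at a visit is determined after randomisation, and in an open-label trial attendance timing could differ by arm.

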### Blinding

This will be an open-label trial owing to the nature of the intervention. The outcome will be collected by a research coordinator who will be blinded to intervention assignment and will not be involved in recruitment and rehabilitation care of the participant.

### Outcomes

Primary outcome: Early recovery of knee function is one of the desired outcomes by patients undergoing knee arthroplasty.^14^ The primary outcome knee function will be assessed using the ADL subdomain of Knee Injury and Osteoarthritis Outcome Score (KOOS). It is a validated tool to evaluate post knee rehabilitation interventions^15^ and will be completed by the trial participants at baseline (before surgery status), 3 and 6 months after surgery in both groups. The total score ranges between 0 and 100 and the minimum clinically important group difference for this domain ranges from −1.5 to 15.5 units.^16^ The KOOS-ADL questionnaire will be self-administered in paper during the follow-up visit by the patient. If the patient is not able to complete it by self, then the family member will assist in eliciting the responses from the patient. In the absence of a family member, an independent assessor, not involved in the intervention implementation and rehabilitation, will administer the questionnaire. The primary comparisons would be to compare the end value of KOOS-ADL score at 3 and 6 months independently between the two groups adjusted for baseline score.

Secondary outcomes: Other quantitative outcomes include pain, assessed using the nine-item KOOS-Pain questionnaire^15^ with a 5-point ordinal response scale, higher scores indicating higher levels of pain. Activity level will be assessed using the lower extremity activity scale,^17^ a single item self-reported question with 18 states of activity, higher numbers indicating higher level of activity. Quality of life will be assessed using the EuroQoL-5 Dimensions-5 Levels questionnaire,^18^ capturing five domains of health, namely mobility, self-care, usual activities, pain/discomfort and anxiety/depression. The overall score ranges from 0 to 1, higher score indicating better quality of life. Safety, knowledge about recovery, rehabilitation adherence, satisfaction with surgical outcome and cost incurred will be collected using study-specific questionnaires. Active and passive knee ROM^19^ of the operated knee(s) will be measured using a digital goniometer. Performance-based measurements include chair rising test to assess lower limb strength, stair climbing and 6 min walk tests to assess knee function, timed-up and go to assess gait stability,^20^ and single leg stance to assess balance.^21^ Further explanation of the measurement tools is found in table 2 and the standardised procedure to conduct the performance-based tests is illustrated in online supplemental efigure 8.

**Table 2 T2:** Trial outcomes and schedule of data collection

	Study period					
Time point	Enrolment	Baseline (0)		Visit 1 (3 months)		Visit 2 (6 months)
Screening	X		Telephonic health check-in		Telephonic health check-in	
Informed consent	X					
Health history (comorbidities)		X				
Randomisation	X					
Patient-reported outcome measures						
Knee function*		X		X		X
Knee pain†		X		X		X
Activity level‡		X		X		X
Quality of life§		X		X		X
Knee range of motion¶		X		X		X
Safety** (falls and rehospitalisation)				X		X
Knowledge about recovery††				X		
Rehabilitation adherence‡‡				X		
Cost incurred by patients§§				X		X
Satisfaction with surgical outcome¶¶						X
Performance based measures*** Function (SCT, 6MWT), Gait stability (TUG), Lower limb strength (CRT), Balance (SLS)				X		X
Process indicators††† Implementation fidelity and reach of the intervention, app usage, barriers and facilitators to implementation and end user satisfaction.						

* Knee function assessed using the Activities of Daily Living subdomain of KOOS, a self-reported 17-item questionnaire with 5-point ordinal scale responses, with score ranging from 0 to 100, higher score indicating better knee function.

† Knee pain will be assessed using the pain subdomain of KOOS (9 items) with 5-point ordinal scale responses. Score ranging from 0 to 100, higher score indicating severity of pain.

‡ Activity level assessed using lower extremity activity scale a single item question with 18 states of activity levels, higher level indicating higher activity.

§ Quality of life assessed using EQ-5D-5L, a 5-item questionnaire capturing 5 domains-mobility, self-care, usual activities, pain/discomfort, and anxiety/depression. The score ranges from 0 to 1, higher score indicating better quality of life. Additional Visual Analogue Scale for rating current state of health (0–100).

¶ Knee range of motion-active and passive flexion and extension of operated knee(s) using digital goniometer in supine position.

** Safety—number of falls after discharge to home as reported by the family or patient and number of rehospitalisations due to index knee surgery.

†† Knowledge about recovery-14 item studyp-specific questionnaire.

‡‡ Rehabilitation adherence-22-item study-specific questionnaire.

§§ Cost incurred by the patient after surgery for physiotherapy services and medications, travel, re-hospitalisation and potential productivity loss.

¶¶ Satisfaction with surgical outcome—8-item Likert scale questionnaire.

*** Performance based measures—SCT measured as time in seconds to complete climbing up and down 12 steps of 18 cm in vertical height; 6 minute walk testT-Distance covered in 6 min at self-paced walking; TUG- Time (in secs) taken to rise from a chair of 44 cm height, walk for 3 m, turn back and be seated on the same chair. CRT-number of repetitions in 30 s to raise rising chair of 44 cm height; SLS—time in seconds an individual can stand on a single leg with eyes open.

††† Process indicators will be assessed by triangulating the findings from the screening logs, research coordinator observations, app analytics data and qualitative interviews with the end users.

CRT, chair rising test; EQ-5D-5L, EuroQol-5 Dimensions-5 Levels; KOOS, Knee Injury and Osteoarthritis Outcome Score; 6MWT, 6 Minute Walk Test; SCT, stair climbing test; SLS, single leg stance; TUG, Timed Up and Go.

Process evaluation outcomes: Fidelity of the intervention and app usage by the patient and healthcare provider will be documented using a checklist. The data for this checklist will be extracted from the research coordinators’ notes and backend app analytics on app usage, by a member of the research team not involved in participant recruitment and follow-up. The reach of the intervention will be assessed from the screening logs. Contextual factors that act as facilitators and barriers for implementing this intervention and acceptability of the intervention will be collected through a semistructured interview with the end-users. To gain understanding of the mechanistic pathway to change, we will measure self-efficacy to rehabilitation. This questionnaire was developed based on the rehabilitation adherence questions designed for sports-related knee injury by Shin *et al*.^22^ However, our questionnaire is not validated for all the psychometric properties. We will also record knowledge on recovery after surgery using a set of knowledge questions and collect the list of exercises performed from both the groups.

Economic component: Resource use from patient perspective that includes cost of physiotherapy services, travel expenditures and wages lost due to clinic visits will be measured using study-specific questionnaires at 3 and 6 months in both groups. Health-related quality of life will be measured using EQ-5D-5L^18^ to measure quality-adjusted life-years (QALYs).

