#### Secondary objectives

The key secondary objectives are to compare the superiority of app-based rehabilitation versus usual home-based rehabilitation in patients undergoing arthroplasty for knee arthritis for knee pain, knee ROM, gait speed and stability, balance, lower limb strength and lower extremity activity at 3 and 6 months. Safety outcomes include falls and knee-related hospital readmissions.

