A research coordinator will be available at clinical site to provide any technical assistance to the clinical team who will also have access to the dashboard to track the overall progress with the programme. Adherence to the intervention by patients will be assessed by the number of times they complete the diary, number of successful video consultations. Once a month check-in phone calls will be made to assist with any difficulty in using the app. Adherence to interventions by healthcare providers will be assessed by the number of scheduled video calls, and the number of times exercises have been updated.	There are no ways in usual care to monitor patient adherence to the rehabilitation protocol. However, to ensure trial participants are not lost to follow-up a monthly check-in call will be made to remind them about the follow-up visit.

TReAT, TeleREhabilitation after knee ArThroplasty.

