### Participant retention strategies

The research coordinator involved in recruitment will telephonically contact the trial participants of both groups at least once a month for rapport building and to enquire about their health. For the app group participants, any technical query related to the app will also be resolved. Travel reimbursements will be provided to trial participants at 3-month and 6-month visits, as per the clinical site ethics committee’s recommendation. We will share a newsletter in English and Hindi every 2 months with all trial participants to provide an update on trial progress and encourage them to visit the hospital for their trial related follow-up. If a participant is unable to make it to the hospital for a follow-up visit, participant reported outcome measures will be collected telephonically and the participant will be motivated to visit the hospital at the earliest for conducting the performance-based measurements.

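### Falls and readmissions are scheduled for recording only at the 3- and 6-month visits; falls rest on about three months' recall and may be under-counted, although both arms are phoned at least monthly

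*Protocol article*

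**What the plan says.** All references are to the protocol article.

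- **Safety outcomes.** Secondary objectives: "Safety outcomes include falls and knee-related hospital readmissions". Table 2 marks the safety row at Visit 1 (3 months) and Visit 2 (6 months) only. The two telephone health check-in columns carry no safety mark.
- **Source.** The Table 2 footnote counts falls as the "number of falls after discharge to home as reported by the family or patient" and readmissions as the "number of rehospitalisations due to index knee surgery". The Outcomes text adds: "Safety, knowledge about recovery, rehabilitation adherence, satisfaction with surgical outcome and cost incurred will be collected using study-specific questionnaires".
- **Monthly calls.** Under Participant retention strategies, the recruiting coordinator "will telephonically contact the trial participants of both groups at least once a month for rapport building and to enquire about their health". Table 1 (How well) describes the calls by arm. For the app arm: "Once a month check-in phone calls will be made to assist with any difficulty in using the app". For usual care: "a monthly check-in call will be made to remind them about the follow-up visit".
- **Who collects outcomes.** Under Blinding, the collector is a coordinator who does not know the allocation and takes no part in recruitment or rehabilitation care.
- **Missed visits and loss.** Under Participant retention strategies, participant-reported measures are taken by telephone from anyone who cannot attend. Under Statistical methods, the modified intention-to-treat set requires at least one follow-up visit and leaves out those lost after enrolment.
- **Oversight.** Under Trial management, no data safety monitoring committee was appointed.

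**The concern.** Safety is one of the trial's declared aims, and falls and knee-related readmissions are the only safety outcomes the article names. With no monitoring committee, these two counts carry most of the safety evidence.

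A fall without lasting injury is easy to forget over three months. The trial already speaks to every participant about three times in that interval, yet the published schedule does not use those contacts to record events. A patient who falls or is readmitted in the first weeks, mentions it on a call and is then lost altogether may leave no trace in the safety results. What is at stake is how complete the safety counts are. The primary analysis is not affected.

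**Working it through.** **1. Recall interval.** Discharge is typically 48–72 hours after surgery (Study setting). Safety is then asked at 3 and 6 months. If the 6-month questionnaire covers the time since the 3-month visit (an assumption; the article does not say), each window is about 3 months. Asking at monthly calls would cut it to about 1 month.

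**2. Contacts already planned.** With 300 participants:
- calls, at one per month for 6 months: 6 × 300 = 1,800
- calls, if two of the six coincide with visits: 4 × 300 = 1,200
- visit safety records, at most: 2 × 300 = 600

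**3. Possible under-count.** The plan states no fall rate, readmission rate or recall accuracy, so there is no safety figure to reproduce. The evaluable number per arm follows from the Sample size section: 150 × (1 − 0.10) = 135. Fallers seen = 135 × risk × capture. The risks and the 80% capture below are assumed.

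| Assumed true risk | True fallers per 135 | Seen at 80% capture | Risk ratio if equal in both arms |
|---|---|---|---|
| 5% | 6.75 | 5.4 | 1.00 |
| 10% | 13.5 | 10.8 | 1.00 |
| 20% | 27.0 | 21.6 | 1.00 |

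Equal under-capture lowers both counts and leaves the ratio alone.

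**4. What unequal capture would do, if it occurred.** With no true difference, the observed risk ratio equals the ratio of capture rates (all assumed):
- 80% v 75%: 0.80 / 0.75 = 1.07
- 90% v 75%: 0.90 / 0.75 = 1.20
- 90% v 70%: 0.90 / 0.70 = 1.29, or 0.70 / 0.90 = 0.78 if reversed

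For scale, take 15% true risk with 90% v 75% capture: 135 × 0.15 × 0.90 = 18.2 and 135 × 0.15 × 0.75 = 15.2 fallers. Using 18 v 15, the standard error of the log risk ratio is √(1/18 − 1/135 + 1/15 − 1/135) = 0.33. The 95% interval around 1.20 is about 0.6 to 2.3, so a bias of this size would sit well inside sampling error.

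**5. Patients lost.** Planned loss is 10% of 300 = 30. This is a ceiling on patients with missing safety data, for three reasons:
- the telephone back-up covers those who merely miss a visit
- someone lost after month 3 has already given one report
- falls are counted from discharge, so someone who misses month 3 may still report them at month 6

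**6. Does the plan itself show unequal capture?** The formal collection is the same in both arms: one questionnaire, the same visits, a blinded collector. The app arm has much more contact (Table 1: daily monitoring to one month, weekly to three months, diary, messaging, video consultations). However, falls are not among the listed diary items, and nothing says that app messages feed the safety count.

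**The case against.** The strongest reply is that this is a condensed article. The calls are described as health check-ins, and what is logged on them belongs to the case report form or the full protocol. The blank check-in columns of Table 2 hold no mark for any outcome, so they are weak evidence that safety is ignored. This stands in part: a reader might infer that no safety item is collected at the calls, but the article is silent rather than explicit. The published schedule nevertheless places safety at two visits only, so the point is more than an omitted detail.

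Four other stronger readings are tempting, and the document does not support them.

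- **Events are under-counted as a fact.** No event rate or recall accuracy is given. It is a reasonable expectation for falls, and its size is unknown.
- **The arms are captured unequally.** The formal collection is symmetric and blinded. Table 1 gives the calls a different purpose by arm, but the retention section gives a common purpose and adds app queries in one arm. Extra contact makes unequal capture possible; it does not demonstrate it.
- **Anyone who misses the 3-month visit gives no safety data.** Table 2 lists safety under the patient-reported measures, which are taken by telephone when a visit is missed. Such patients are probably covered.
- **Readmissions also rest only on recall.** The reporting source is attached to falls. Rehospitalisation is also asked for in the cost data, which gives a second prompt, and an admission is harder to forget.

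The fix also has a real drawback. The caller is the recruiting coordinator and a research coordinator performs the randomisation, so the caller probably knows the allocation. Making calls the main source would trade blinded for unblinded ascertainment. That objection stands, and it limits how call data should be used.

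**Conclusion.** The point holds in a limited form. The published schedule rests fall counts on about three months of patient or family recall. It may also miss events in patients later lost to all follow-up, although at least monthly health calls in both arms could capture them.

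The size cannot be derived from the article. Under assumed equal capture of 80%, one faller in five goes uncounted and the risk ratio is unaffected. Risk ratios of 1.07 to 1.29 would need capture rates that differ between arms, which is assumed here and not shown. Thirty patients is a ceiling on those without complete safety data at the planned loss; the number with none should be smaller.

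The modified intention-to-treat definition appears under effectiveness outcomes, and the article states no separate safety set. If that definition also governs safety, patients lost before any visit drop out of the safety report. The change is worth making because it is cheap and serves a stated aim. If the full protocol already logs events at calls, it is enough for Table 2 to say so.

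**What to change.** 1. Add safety to the two telephone health check-in columns of Table 2.
2. At each monthly call, ask the same closed questions in the same words in both arms: any fall since the last contact (number, dates) and any hospital admission (date, reason). Record the answers in REDCap.
3. Keep the blinded assessor's 3- and 6-month questionnaire as the source for the between-arm comparison. Use the call log to prompt confirmation at the visit and as a supplementary source.
4. Report falls and readmissions descriptively for all randomised patients with any post-discharge contact, not only those with a follow-up visit.

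**Cost.** A short REDCap form and a minute or two on calls already being made; no extra visits, staff or sample size. The caller is probably unblinded, which the identical script and item 3 contain but do not remove. Recruitment was planned to run from June 2024 to December 2025, with data collection to June 2026, so patients already past their calls will have visit data only. The report should say from what date call data were collected.
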